### Cardiovascular Rehabilitation (CVR) program

The CVR program included in this study is typical of most contemporary phase II cardiac rehabilitation programs in Australia [14, 39]. The CVR program is multidisciplinary, time-limited (once a week, 6-weeks), conducted in groups, health service-based, and has educational and supervised exercise components (one hour education plus one hour exercise per week). Members of the multidisciplinary team include exercise physiologists, physiotherapists, dietitians, psychologists, pharmacists and supervised university health students. The intention of the CVR program is not to replace other treatment services that may be required after a mild stroke to address any deficits such as speech or motor impairments but rather provide a comprehensive program for CVD risk factor modification and management.

The main aim of the exercise sessions will be to increase exercise capacity by exercising large muscle groups at a moderate intensity [14]. The best predictor of an increased risk of death from any cause in men with cardiovascular disease is exercise capacity [40]. For every 1-MET increase in exercise, there is a 9% improvement in survival [40]. The exercise sessions will be conducted in the same way as a typical cardiac rehabilitation program as many cardiac rehabilitation participants have co-morbidities, including stroke [41]. All exercise sessions will be individually tailored for each of the participants, including aerobic and resistance training, and supervised by a physiotherapist and/or exercise physiologist.

Members of the multi-disciplinary team will conduct education sessions to increase the participant’s knowledge of their CVD condition and increase self-management skills for risk factor management. The education will be slightly modified compared to a typical cardiac rehabilitation program to include the anatomy and physiology of the brain, TIA and ischaemic stroke, and the management of stroke risk factors. The education sessions will cover: cardiac and brain anatomy and physiology; cardiac and stroke risk factors, modification and management of symptoms; how to deal with stress, anxiety and depression; cardiac and stroke medications; benefits of exercise and physical activity; and nutrition advice. People with heart disease will be recruited to this program to replicate a standard phase II cardiac rehabilitation program currently offered in Australia and to enable the integration of people with TIA, mild stroke, and heart disease in the same program. However, research outcomes will not be collected or analysed for this group as the evidence base for exercise-based cardiac rehabilitation for people with heart disease is well established [17].

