### Randomisation

An investigator not involved in recruitment or assessments will use a computer-generated random number sequence, with participants allocated in a 1:1 ratio. Group allocation will be concealed using sealed, consecutively numbered opaque envelopes. Following each participant’s baseline assessment, the next envelope in the sequence will be opened to reveal random allocation to one of two groups: the Cardiovascular Rehabilitation program or the 6-month wait-list control group.

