### Usual care control group

Those randomised to the control group will participate in usual care following a TIA or mild stroke. In Australia, this typically consists of follow-up with a neurologist and little or no secondary prevention other than pharmacological management [42]. Control participants will be wait-listed for the CVR program and will commence the CVR program 6-months after they have completed their baseline measures.

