### Sample size

The sample size calculation for the 2-arm randomised control trial is based on an increase in 6MWT-distance as a result of aerobic exercise programs similar in design to cardiac rehabilitation exercise programs for survivors of stroke [58]. This systematic review and meta-analysis found an effect size of 0.41 (Hedges’ g corrected effect size) for 6MWT-distance. With a Cohen’s f = 0.205 (half Hedges’ g), three repeated measures (baseline, 6-weeks, and 6-months), a two-sided significance test at a 5% alpha level, a power of 80%, and assuming 0.5 as the correlation among repeated measures, the total sample size required is 128 (64 per arm), calculated using G*Power version 3.1.9.4. Assuming an 8% drop-out rate as commonly found in stroke research [59], the final sample size is 140, with 70 in each group.

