### Data analyses

All participants who complete the baseline assessment and attend at least one CVR session will be included in the analysis. Descriptive statistics will be completed, and feasibility measures will be reported as percentages. Data will be analysed according to group assignment for participants with TIA or mild stroke following intention-to-treat principles. To analyse 6MWT-distance and all other secondary outcomes, methods for repeated measures analysis will be used. Linear (for continuous outcome data) and Generalised Linear (for Binary and Count outcome data) mixed-effects models for repeated measures will be used for between-within group comparisons and time-interactions analyses adjusting for demographic characteristics and other potential covariates, such as time since TIA or mild stroke. All analyses will be conducted using either SPSS or STATA. Any estimate will be reported with associated 95% confidence intervals. Significance level will be set at p < 0.05.

Implementation outcomes will be evaluated using both quantitative and qualitative methods. The Reach, Effectiveness, Adoption, Implementation, Maintenance (RE-AIM).

framework will be used to assess implementation outcomes such as characteristics of participants (reach), change in 6-min walk distance (effectiveness), number of referrers and characteristics of CVR program clinicians (adoption), fidelity and cost of the intervention (implementation) and drop-out rates (maintenance) [60]. A qualitative thematic analysis of semi-structured interviews from both participants and health professionals involved in the CVR program will also be undertaken. Two research team members will independently code and identify potential themes using an inductive thematic approach [61]. Emerging themes will be discussed until consensus is reached on final themes and categories. Deductive analyses will be mapped to the Consolidated Framework for Implementation Research (CFIR) [62] constructs to understand how the CVR program works and factors that influence implementation success or failure. The Intervention Characteristics and Inner Settings domains will be primarily considered as they are more relevant for this type 1 effectiveness-implementation hybrid trial.

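### The sample size makes no allowance for correlation within CVR classes, which can arise in one arm only, and the analysis text names no class effect

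*Protocol article*

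**What the plan says.** Participants are randomised individually, "with participants allocated in a 1:1 ratio" (Randomisation). The intervention is "time-limited (once a week, 6-weeks), conducted in groups, health service-based, and has educational and supervised exercise components", with one hour of education and one of exercise each week (Cardiovascular Rehabilitation (CVR) program). Within the sessions the exercise is personal: "All exercise sessions will be individually tailored for each of the participants, including aerobic and resistance training, and supervised by a physiotherapist and/or exercise physiologist". The classes are mixed: "People with heart disease will be recruited to this program to replicate a standard phase II cardiac rehabilitation program currently offered in Australia".

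The control arm has no classes during the comparison: "Control participants will be wait-listed for the CVR program and will commence the CVR program 6-months after they have completed their baseline measures" (Usual care control group).

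The Sample size section starts from a meta-analysis that "found an effect size of 0.41 (Hedges’ g corrected effect size) for 6MWT-distance". It takes half of this as Cohen's f, adds three measurements, a within-person correlation of 0.5, two-sided 5% alpha and 80% power, and concludes that "the total sample size required is 128 (64 per arm". An 8% drop-out allowance brings the total to 140. No class size, class ICC or design effect appears.

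The Data analyses section says that "mixed-effects models for repeated measures will be used for between-within group comparisons and time-interactions analyses", adjusted for demographic and other covariates. No class, cohort or therapist effect is named.

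**The concern.** This is an individually randomised trial with group treatment in one arm. People in the same class share education sessions, classmates and supervision, so their outcomes may be more alike than those of people in different classes. Controls have no such grouping. The 0.5 correlation in the sample size is between visits of one person and does not cover this.

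If class correlation exists and the model omits it, confidence intervals are too narrow and nominal significance is too easy to reach. If the model includes it, the test is valid but has less power than planned. Secondary outcomes may be more exposed than walking distance. The shared education covers stress, anxiety, depression, physical activity and nutrition, which HADS, AQoL-6D and accelerometer activity could reflect, and these outcomes are analysed with the same family of models.

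**Working it through.** **1. Reproduce the stated figure.** For a between-groups repeated-measures test, the noncentrality is λ = f² × N × m / (1 + (m − 1)ρ). The article's inputs are f = 0.205, N = 128, m = 3 visits and ρ = 0.5. So λ = 0.042025 × 128 × 3 / 2 = 8.07. With 1 and 126 degrees of freedom the power is 0.805, and 128 is the smallest even total that reaches 80%. Then 128 / 0.92 = 139.1, which gives 140 with equal arms. The formula has no term for class, so it sets the class ICC to zero.

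**2. Class size (assumed).** Recruitment runs for 18 months, about 78 weeks. If one closed class runs at a time, 78 / 6 = 13 classes and 64 / 13 = 4.9, or about 5 trial participants per class. The article states neither closed classes nor one class at a time, so 3 and 10 per class are shown as well.

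**3. Effect of clustering in one arm.** With c trial participants per class, the CVR-arm variance is multiplied by DE = 1 + (c − 1) × ICC. With equal arms:

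- true SE / unadjusted SE: R = √((1 + DE) / 2)
- type I error of the test that ignores class: 2 × (1 − Φ(1.96 / R))
- power of a correctly sized test at 64 per arm: Φ(2.84 / R − 1.96)

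Here 2.84 = 0.41 / (√(2/3) × √(2/64)), where √(2/3) is the SD of the three-visit average at ρ = 0.5.

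Example with c = 5 and ICC 0.05: DE = 1.20 and R = √1.10 = 1.049. Type I error is 2 × (1 − Φ(1.869)) = 6.2%, and power is Φ(2.708 − 1.96) = 77%.

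| c | ICC | R | Type I error, class ignored | Power, correctly sized test | Total N incl. 8% drop-out |
|---|---|---|---|---|---|
| any | 0 | 1.000 | 5.0% | 81% | 137 |
| 3 | 0.01 | 1.005 | 5.1% | 81% | 137 |
| 3 | 0.05 | 1.025 | 5.6% | 79% | 144 |
| 3 | 0.10 | 1.049 | 6.2% | 77% | 150 |
| 5 | 0.01 | 1.010 | 5.2% | 80% | 140 |
| 5 | 0.05 | 1.049 | 6.2% | 77% | 150 |
| 5 | 0.10 | 1.095 | 7.4% | 74% | 164 |
| 10 | 0.01 | 1.022 | 5.5% | 79% | 144 |
| 10 | 0.05 | 1.107 | 7.7% | 73% | 168 |
| 10 | 0.10 | 1.204 | 10.4% | 66% | 198 |

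The normal approximation gives 137 at ICC 0, against the plan's 140 from the F test.

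**4. Check by simulation** (40,000 replicates, 64 per arm, classes of 5). The test that ignores class rejected a true null in 5.2%, 6.1% and 7.2% of replicates at ICC 0.01, 0.05 and 0.10, in line with the table. Its own power was 80.0%, 79.5% and 78.9%.

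**5. A simplification.** The ICC is applied to the three-visit average, although baseline precedes the classes. For follow-up average minus baseline, the variance at ρ = 0.5 is 0.75 + 1 − 2 × 0.5 = 0.75. A class effect that persists at both follow-ups, with a single-visit ICC of 0.05, then acts like 0.05 / 0.75 = 0.067. At c = 5 this gives DE = 1.267, R = 1.065 and a type I error of about 6.6%.

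**The case against.** A reader might infer that the plan treats all participants as independent, so that its standard error is too small and its 5% and 80% do not hold. The documents do not support that. The Data analyses section never states independence and does not give the random-effects structure, which a journal article commonly leaves to a fuller protocol or SAP. Omission of class from the model is an inference from silence. Its omission from the sample size is firm.

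The size is also uncertain, and a small ICC is plausible for walking distance. The test is individual, the exercise is individually tailored, and staff common to all classes at a single centre add no variance between classes. Heart disease patients take places, so trial participants per class may be few. At ICC 0.01 with 3 to 5 per class, type I error is 5.1% to 5.2% and power 80% to 81%, which is negligible.

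Closed classes are not stated either. Recruitment is staggered and allocation follows each person's own baseline, so entry may be rolling and class membership may overlap. A single nested class effect would then only approximate the structure.

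Finally, it is tempting to read 7.4% type I error and 74% power as the performance of one analysis. They belong to different tests. A test that ignores class loses little power (78.9% in simulation at ICC 0.10 with 5 per class) but has an inflated error rate. A correctly sized test holds 5% and loses the power.

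What survives is that treatment is grouped in one arm only, that N is fixed with no allowance for it, and that the analysis text names no class effect.

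**Conclusion.** The point holds conditionally. The stated 128 is correct for a class ICC of zero and has almost no slack (power 0.805). If the ICC is positive and class is left out of the model, the standard error is too small by an amount that the documents do not determine. With an assumed 5 per class and ICC 0.01 to 0.10, the result is either a type I error of about 5.2% to 7.4% (class ignored) or power of about 80% to 74% (class modelled correctly). The full assumed range runs from no practical effect (3 per class, ICC 0.01) to a material one (10 per class, ICC 0.10: type I error 10.4%, or power 66%). These figures assume closed classes of equal size and a normal approximation. This is an inexpensive improvement to the plan, not a demonstrated failure of it.

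**What to change.** 1. Record each CVR participant's class or start cohort. The Feasibility section lists the number of sessions attended, but not which class.
2. Fit the 6MWT model and the other outcome models with a class random effect in the CVR arm only, with each control as a singleton. Use Satterthwaite or Kenward-Roger degrees of freedom for the linear models.
3. If entry is rolling and classes overlap, define the cluster by start cohort and report this as a sensitivity analysis.
4. State in the Sample size section that 128 assumes no class clustering, and give power over ICC 0 to 0.10 with the assumed class size.

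The cost is one recorded variable, one model term and a sentence or two. Intervals become slightly wider, and about 1 to 2 points of power are lost if the ICC is really zero. No extra participants are needed for the change itself, but it only discloses a power shortfall and does not cure it. At 5 per class, restoring 80% power would take about 150 participants at ICC 0.05 or 164 at ICC 0.10, against the planned 140.

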### Usual care control group

Those randomised to the control group will participate in usual care following a TIA or mild stroke. In Australia, this typically consists of follow-up with a neurologist and little or no secondary prevention other than pharmacological management [42]. Control participants will be wait-listed for the CVR program and will commence the CVR program 6-months after they have completed their baseline measures.

### Outcome measures

All outcome measures will be collected at baseline, 6-weeks, and 6-months. Assessor blinding to group allocation will be used throughout the study. Research assistants will collect all outcome measures following training, using a standardised protocol and the same research grade equipment.

The primary outcome measure will be distance completed in the 6-min walk test and reported as metres (functional exercise capacity). Secondary outcome measures include daily minutes of accelerometer moderate-to-vigorous physical activity, body mass index, waist circumference, blood pressure, quality of life (AQoL-6D), anxiety and depression (HADS) and unplanned cardiovascular disease-related emergency department and hospital admissions. Qualitative data will be collected from participants and health professionals at the end of the intervention period, and cost analyses will be conducted. Demographic and clinical information will be collected using a questionnaire, including questions on sociodemographic variables (e.g., gender, age, education level) as well as clinical predictor variables (e.g., stroke-related medication, other medical conditions, smoking status). The research assistants will also record participant admission diagnosis and date of event or intervention details.

#### Functional exercise capacity

The 6-min walk test (6MWT) is a commonly used objective measure of functional exercise capacity in cardiac rehabilitation and stroke [43, 44]. The distance an individual is able to walk along a flat 25–30 m walkway over a 6-min period, with breaks as required, will be recorded. Only one trial will be administered. The test is a self-paced, submaximal test of exercise capacity, and has been found to have a moderate-to-high reliability and validity [44]. A change in distance of 34 m is considered a clinically meaningful change in people post stroke [43].

#### Physical activity levels

A triaxial commercial accelerometer (ActiGraph GT3X, Fort Walton Beach, FL) will be used to objectively assess physical activity. Accelerometers allow an objective measurement of quantity and intensity of movement and have been found to be reliable and valid [45]. Participants will be asked to wear the monitor on their right hip during a typical week while awake for 7-consecutive days. All data will be sampled and downloaded as raw data (30 Hz), converted to 15-s epochs (time interval), and then counts per minute (cpm) using the Actilife software [46, 47]. A ‘count’ is the unit of measure for activity for ActiGraph’s activity monitors [48]. Data will be screened, excluding data if: < 10 h per day wear time (non-wear defined as > 60 consecutive minutes where there is zero activity, with no allowance of epochs with counts above zero) and less than 4 days of valid data [46, 47, 49]. The Sasaki vector magnitude 3 cut-points will be used to determine time spent in MVPA (≥ 2690 cpm) [46, 47, 49, 50]. To measure sedentary behaviour, the vector magnitude cut-point will be used (< 150 cpm), categorizing light physical activity (LPA) as 150–2689 cpm [46, 47, 49, 51]. Estimating daily time spent in physical activity and sedentary behavior will be calculated by dividing the total time spent (minutes) in each threshold by the number of valid days.

#### Anthropometric characteristics and blood pressure

Height (m), weight (kg) and body mass index (BMI; kg/m^2^) will be recorded using a calibrated set of scales and a stadiometer. Waist circumference will be measured in centimetres using a stretch-resistant tape measure. The waist circumference will be recorded as the midpoint between the lower margin of the lowest palpable rib and the top of the iliac crest [52]. Blood pressure will be obtained using a sphygmomanometer (Welch-Allyn DS66) on the right arm of seated subjects. Waist circumference and blood pressure measurements will be repeated twice, and the average will be recorded.

#### Health-related quality of life

Health-related quality of life will be assessed using the Assessment of Quality of life (AQoL-6D). The AQoL-6D was developed in Australia and uses Australian importance weights [53]. The AQoL-6D is self-administered and consists of 20-items covering: independent living, mental health, coping, relationships, pain and sense. A multi-attribute utility score is then obtained, where a score of 100 reflects best health. The AQoL-6D is reliable and valid in community settings and can be used in economic analyses [54, 55].

#### Anxiety and depression

The Hospital Anxiety and Depression Scale (HADS) will be used for the assessment of anxiety and depression [56]. This questionnaire is a 14‐item self‐reporting questionnaire comprised of 4‐point Likert‐scaled items covering the occurrence of symptoms of anxiety (HADS‐A) and depression (HADS‐D) over the past 2 weeks. Each item on the questionnaire is scored from 0–3, so that a person can score between 0 (best outcome) and 21 (worst outcome) for either anxiety or depression. The minimally clinically important difference for patients with CVD is 1.7 [57].

#### Hospital admissions and emergency department visits

Participants will be surveyed at 6-weeks and 6-months to determine if they have had any unplanned hospital admissions or presentations to the emergency department during the study period. This information will then be verified, where possible, by hospital patient admission records to ascertain the Australian Refined Diagnosis Related Group (AR-DRG) and Urgent Related Group (URG) classification code assigned to the admission.

#### Qualitative perceptions of the CVR program

Qualitative data will be collected from the intervention participants. Semi-structured interviews will be conducted by a member of the research team (audio-recorded and professionally transcribed), investigating participants’ views on the acceptability of the intervention, including ease of attendance, satisfaction, and motivation. Interviews will be continued until the team is confident that no new ideas were being raised in the interviews.

At the completion of the CVR program health professionals involved in the program and referring to the CVR program will also be invited to take part in semi-structured interviews to investigate their views on the acceptability, value, and impact of the CVR program within health service delivery, as well as referral pathways. This data will be analysed and used to inform the integration of people with TIA and mild stroke into existing cardiac rehabilitation services, including the development of pathways to facilitate referrals to these services.

#### Feasibility

Data will be collected on participant recruitment rates, adherence to the program (number of exercise and education sessions attended), number of dropouts, and the number lost to follow-up. Any adverse events experienced during the program will also be recorded. If an adverse event occurs whilst the participant is taking part in the study, they will be managed immediately in line with university and health services policies and procedures. If there is an adverse event that is related to the intervention, the study coordinator will be made aware of group allocation and will discuss continuation of the participant’s involvement with the research team. Any adverse events will be reported to the ethics committee, advisory group and the participant’s medical team.

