**Methods:**

This type 1 effectiveness-implementation hybrid study will use a 2-arm single-centre assessor-blind randomised controlled trial design, recruiting 140 participants. Adults who have had a TIA or mild stroke in the last 12-months will be recruited by health professionals from hospital and primary healthcare services. Participants will be assessed and randomly allocated (1:1) to the 6-week CVR program or the usual care 6-month wait-list control group. Distance completed in the 6-min walk test will be the primary effectiveness outcome, with outcomes collected at baseline, 6-weeks (complete CVR) and 6-months in both groups. Other effectiveness outcome measures include unplanned cardiovascular disease-related emergency department and hospital admissions, daily minutes of accelerometer moderate-to-vigorous physical activity, body mass index, waist circumference, blood pressure, quality of life, anxiety and depression. Implementation outcomes will be assessed using the Reach, Effectiveness, Adoption, Implementation, Maintenance (RE-AIM) framework, including a cost-effectiveness analysis. Semi-structured interviews will be conducted with participants and CVR program health professionals, investigating the acceptability, value, and impact of the CVR program. Qualitative analyses will be guided by the Consolidated Framework for Implementation Research.

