## Methods

### Design

The type 1 effectiveness-implementation hybrid study [36] will use a 2-arm single-centre assessor-blind randomised controlled trial design and will be conducted in Canberra, Australia, commencing in 2022 (Fig. 1). People with TIA and mild stroke will be randomised to a 6-week exercise-based Cardiovascular Rehabilitation (CVR) program or a usual care 6-month wait-list control group. Recruitment will be staggered over 18-months and the total study duration for each participant will be 6-months from commencing the study.

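### Adverse events are recorded only during the CVR program, so events without hospital or emergency department contact cannot be compared between the arms

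*Protocol article*

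**What the plan says.** Adverse events are handled in one paragraph of the protocol article, under Feasibility, next to recruitment, adherence and drop-out.

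- Recording: "Any adverse events experienced during the program will also be recorded".
- Management: "If an adverse event occurs whilst the participant is taking part in the study, they will be managed immediately".
- Reporting: "Any adverse events will be reported to the ethics committee, advisory group and the participant’s medical team".

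Other sections fix who is in the program and when.

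- The Cardiovascular Rehabilitation (CVR) program section describes it as "time-limited (once a week, 6-weeks").
- The Usual care control group section says that controls "will commence the CVR program 6-months after they have completed their baseline measures".
- The Design section says that "the total study duration for each participant will be 6-months from commencing the study".

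Hospital contact is collected separately. The section on hospital admissions and emergency department visits states: "Participants will be surveyed at 6-weeks and 6-months to determine if they have had any unplanned hospital admissions or presentations to the emergency department". Verification against hospital records follows where possible. The Methods part of the abstract describes the trial "with outcomes collected at baseline, 6-weeks (complete CVR) and 6-months in both groups".

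**The concern.** The recording rule is tied to being in the program. During the randomised comparison only one arm is in the program, and only for its first weeks. An event that a participant deals with at home or with a general practitioner would be written down if it fell within those weeks in the CVR arm. The same event would not be written down in a control, or in a CVR participant after the program ends.

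This matters because the trial is meant to inform whether people with TIA or mild stroke should be brought into existing cardiac rehabilitation services. The plausible harms of a supervised exercise program include falls, strains and exertional symptoms, many of which never reach a hospital. If these are counted in one arm only, the count cannot be read as an excess, because the background rate is not measured. A low count cannot be read as reassurance for the same reason. Analysis cannot repair this, since control events that were never asked about cannot be recovered reliably afterwards.

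**Working it through.** The article gives no figure on adverse events to reproduce. The check sets the windows side by side and then sizes the gap.

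**Inputs**

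- Program length: 6 weeks (CVR program section).
- Start of the program for controls: 6 months after baseline (Usual care control group).
- Follow-up per participant: 6 months (Design).
- Arm size: 70 (Sample size). This agrees with the article's own inflation: 64 / (1 − 0.08) = 69.6, rounded up to 70.
- Assumptions: 6 months is 26 weeks, nobody drops out, and CVR participants start promptly after randomisation.

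**Step 1: the windows by type of event, read literally**

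| Event type | CVR arm, program weeks | CVR arm, after the program to 6 months | Control arm, to 6 months |
|---|---|---|---|
| No admission or emergency presentation | recorded | no stated record | no stated record |
| Unplanned admission or emergency presentation | surveyed | surveyed | surveyed |

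The arms differ only in the first row. Controls enter the program when their 6 months of study participation are over, so anything recorded during their own program falls outside the randomised comparison.

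**Step 2: size of the gap, first row only**

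- Share of CVR follow-up covered: 6 / 26 = 23%.
- Person-weeks covered in the CVR arm: 70 × 6 = 420 of 70 × 26 = 1,820.
- Person-weeks covered in controls: 0 of 1,820.
- Both arms together: 420 / (1,820 + 1,820) = 420 / 3,640 = 11.5%.

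Counting a month as 4 weeks makes the follow-up 24 weeks and the CVR share 6 / 24 = 25%, so the choice hardly matters. If the rule is meant to cover only the sessions themselves, the window shrinks to 6 sessions of 1 hour education plus 1 hour exercise, that is 6 × 2 = 12 hours per participant.

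**Step 3: size for the second row**

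The survey looks back over the study period at 6 weeks and at 6 months, so it is planned to cover all 1,820 person-weeks in each arm.

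**Step 4: do the other adverse-event sentences close the gap?**

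The management and reporting sentences name no arm and are not confined to the program. They say what happens once an event is known. They give no means by which a control's event would become known, and no schedule for asking. Program staff meet CVR participants weekly, while the scheduled assessments of controls after baseline are at 6 weeks and 6 months. Spontaneous reporting would therefore still lean towards the CVR arm.

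**The case against.** The strongest reply is that the more serious harms are already captured evenly. The survey asks about any unplanned admission or emergency presentation, not only cardiovascular ones, and outcomes are collected in both groups to 6 months. A new stroke, a cardiac event or an injurious fall that leads to hospital contact would be found in either arm. This stands. A reader might infer from the recording rule that controls have no comparable record of harm, or that the trial cannot compare harms at all. The documents do not support that, and the 23% and 0% figures must not be quoted as coverage of all harms.

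A second reply is that the management and reporting sentences are study-wide, and that reporting an event presupposes some record of it. This stands in part. It makes the intended window ambiguous, so one cannot say firmly that every control event will go unrecorded. It does not supply systematic collection, and it leaves the paragraph with two different windows.

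A third reply is that a journal article condenses, and that ascertainment detail belongs in the full protocol. That would answer a complaint about missing detail. Here the article states a recording window, and that window differs by arm.

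A fourth reply is that no between-arm table of adverse events is announced, and that the research questions name cardiovascular admissions, not harms in general. That is correct, so one should not claim that a misleading table is planned. It limits the consequence to what the trial will be able to say about events without hospital contact.

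**Conclusion.** The point holds for adverse events that lead to no unplanned admission or emergency presentation. Under the rule as written these are recorded in the CVR arm for about 6 of 26 weeks (23%) and not at all in controls during the randomised period, so they cannot be compared between arms. The size rests on the literal reading of the recording sentence, on 26 weeks for 6 months, on prompt program start and on no drop-out. It does not hold for events with hospital or emergency department contact, which are surveyed in both arms to 6 months. The recording sentence and the management sentence in the same paragraph also need to be reconciled. The sample size is not affected. This is a cheap improvement that should be made, because the difference in ascertainment depends on the arm and cannot be undone at analysis.

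**What to change.** Under Feasibility, replace the two windows with one: adverse events are recorded from randomisation to 6 months in both arms. Add the same adverse-event questions, in the same words for both arms, to the surveys that already ask about admissions at 6 weeks and 6 months. Keep events that occur during sessions as a separate category, and label it in the report as collected in the CVR arm only, so that it is not set against an empty control column.

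The cost is slightly longer surveys and a few more reports to handle. No new visit is needed.
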